## 1.2 Trial rationale

Optimizing asthma management among preschool children is an unmet need since this age group experiences disproportional morbidity and health care utilization compared to school-age children with asthma (14–16). At present, there are insufficient data to recommend additional controller therapies, such as combinations of ICS with LABAs or LAMAs in this age group (37).

[figure not shown]

**Figure 1:** Tiotropium a new treatment option for severe uncontrolled preschool asthma.

Adding Tiotropium to ICS might be a new promising treatment option for severe uncontrolled preschool asthma (41, 42). A recent study in patients aged 1-5 years with preschool asthma showed that the tolerability of Tiotropium + ICS was similar to that of placebo + ICS and demonstrated the potential to reduce asthma-related events compared with placebo (42). This is in line with a recent study of our group. A retrospective analysis of electronic outpatient medical records (Frankfurt University Hospital) was conducted from 2017–2019 to screen for children with persistent asthma treated with ICS + LABA and switched to Tiotropium as add-on treatment, due to severe uncontrolled asthma. 21 children with uncontrolled preschool asthma were compared with 42 children without asthma matched for age, sex, and screening date. There was a significant reduction of hospital admissions, steroid courses, and physician visits when Tiotropium was added to the current medium-dose ICS + LABA treatment (Figure1; Zielen et al. (43).

However, the number of patients included in both studies was small, and further research is required to confirm the beneficial effect on exacerbations in this age group. Additional well-powered trials are needed and called for to further assess the safety and efficacy of Tiotropium in young children before it can be implemented in the current guidelines and disease management plan. Thus assessing its use for treatment in uncontrolled preschool asthma, in whom alternative controller treatments are limited, could be extremely valuable due to the high unmet medical need in this age group (16, 37).

### 1.3 Treatments and rationale for dose selection

A total of 1691 children aged 1–17 years, (560 patients received Tiotropium 5 µg; 559 patients received Tiotropium 2.5 µg; 572 patients received placebo) were treated in five pediatric studies so far (36). Drug-related AEs, those leading to discontinuation and SAEs were very low and balanced between treatment groups, irrespective of age, disease severity, or gender. Interestingly, the FDA in the US licensed 2.5 µg whereas the EMA licensed 5.0 µg Tiotropium for use in patients with asthma. A recent PubMed search including phase 2 and 3 randomized controlled trials (RCTs) evaluated the effects of 2.5 µg Tiotropium on lung function parameters in patients with asthma. The authors found the following: Based on the results of phase 2 and 3 studies 2.5 µg Tiotropium as an add-on to ICS therapy was safe and associated with consistent improvements in lung function in patients with asthma of varying severities across different age groups (44). Accordingly, in the planned study we will use the lower dose of 2.5 µg Tiotropium to be effective and to save cost for better patient care.

#### 1.3.1 Mode and scheme of intervention

Administration of Tiotropium inhalation solution is achieved with the Respimat® inhaler in combination with a drug reservoir/cartridge. All children will use a spacer to inhale Tiotropium Respimat®. No special device will be provided. However, in children < 4 years connected with a face mask and > 4 years connected with a mouth piece. We recently established the age at which children below 5 years are able to handle the Respimat® inhaler and to what degree help may be appropriate (45). A further objective of this study was to acquire inhalation flow profiles depending on the age of the children in the respective "successful handling configuration" (46). The vast majority of children and parents/caregivers were satisfied with operation, instructions for use, handling, and ease of holding the Respimat® inhaler. Although the majority of children aged 4 years could handle the Respimat® inhaler without a spacer, the recommendation is that children below 5 years should use the Respimat® inhaler with a spacer.

### 1.4 Risk-benefit assessment

The favorable benefit-risk ratio based on the so far acquired knowledge about inhaled Tiotropium is the rationale to conduct the study with Tiotropium in preschool asthma. Clinical data in all finished proof-of-concept trials in patients with persistent asthma showed superiority of Tiotropium over placebo treatment with respect to several lung function parameters and also non-inferiority to salmeterol with respect to several lung function tests (47). The same positive add-on effect of Tiotropium on lung function and asthma control was demonstrated in children 6–18 years with moderate and severe asthma (32–35). Accordingly, Tiotropium was licensed as add to ICS in children  $\geq 6$  years addition with severe uncontrolled asthma in Germany 2018. In addition, Tiotropium was safe in all age groups especially in young children (36, 42, 43). In children aged 1-5, a randomised, double-blind, placebo-controlled, phase II/III clinical study in a total of 101 children demonstrated that the number of asthma adverse events was lower for Spiriva Respimat compared to placebo. Exploratory efficacy evaluations did not show differences for Spiriva Respimat from placebo.

Adding Tiotropium to ICS may significantly increase asthma control in this age group. Patients will have fewer symptoms, more symptom-free days, and fewer hospitalizations. Thus, there may be a significant increase of quality of life of patients, parents, and their families.

## **1.5 CONTROL(S) / COMPARATOR(S)**

ICSs are recommended by asthma guidelines as first-line therapy for school-age children. A recent meta-analysis confirmed the beneficial role of ICS among preschool children (7, 16, 27). Consistent with current guidelines all children hospitalized due to an asthma exacerbation will be treated at least with a medium-dose of ICS (Fluticasone 2 x 50 µg). Adding a second or third controller like Montelukast or LABA is allowed.

A placebo group is included in the trial because the absence of such a treatment arm would reduce the reliability of the trial results. In all previous trials in children no untoward serious adverse events happened to patients treated with placebo (on top of maintenance therapy) and the overall incidence of AEs and the incidence of asthma exacerbations, were similar in active treatment arms and in placebo (32–36, 42). Based on these data, and the implementation of a set of rules to withdraw patients with severe asthma deterioration, a placebo treatment group in this trial (on top of maintenance treatment with at least ICS) is considered safe.

## **2 TRIAL OBJECTIVES**

### **2.1 Primary objective**

The primary objective is to evaluate whether addition of Tiotropium via Respimat® to ICS prevents severe asthma exacerbations (defined by hospitalization and/or three consecutive days of oral or parenteral systemic steroid intake or one day of rectal prednisolone application (Rectodelt®).

### **2.2 Secondary objectives**

The secondary objective is to evaluate whether addition of Tiotropium via Respimat® to ICS reduces health utilization (hospitalizations, physician visits, antibiotic use) in partial or uncontrolled preschool asthma.

## **3 TRIAL DESIGN**

This is a prospective randomized, double-blind, placebo-controlled, parallel-group trial (a non-commercial trial, clinical phase III) to evaluate the safety and efficacy of Tiotropium inhalation solution (2.5 µg) administered once daily via Respimat® Inhaler for 52 weeks to prevent severe asthma exacerbations in patients 1–5 years with uncontrolled or partially controlled preschool asthma and at least one severe asthma exacerbation requiring hospitalization and/or was treated with 2 courses of systemic steroids in the last 24 months before visit 1 (three days of oral systemic steroids or one day of rectal prednisolone).

[figure not shown]

**Figure 2:** Trial design

After signing informed consent and completing an initial screening visit (Figure 2, V1), patients enter a 4–6 week screening period to ensure clinical stability (i.e. no severe exacerbations). Patients who meet all inclusion criteria and do not present with any of the exclusion criteria will be randomized into the 52-week treatment period (V2) in which they will be assigned at random to one of the two treatment groups. Additional clinic visits will be scheduled at 6, 16, 28, 40, and 52 weeks after start of therapy (V2). A telephone contact will be scheduled between V4 and V5, V5 and V6, and V6 and V7.

Pulmonary function tests (PFTs) will be performed in patients  $\geq 4$  years who are capable of providing PFTs of acceptable quality. Spirometry/Oscillometry measurements will be performed in patients  $\geq 4$  years if they are capable of providing measurements of acceptable quality (with a mouthpiece) and if the required equipment is available at site.

### 3.1 Trial duration and schedule

The duration of this trial is expected to be 36 months (24 months recruitment, 12 months treatment phase). Patient recruitment is planned to start in February 2022 and end in February 2024. The actual overall trial duration or patient recruitment period may differ from these periods.

### 3.2 Number of patients and trial centers

It is planned to include 152 patients (randomized) in the clinical trial, currently 13 trial sites agreed to participate.

### 3.3 Selection of trial population

A sufficient number of asthmatic patients aged 1–5 years of either sex will be enrolled in the study to ensure that 152 children are entered (randomized) in the trial. Recruitment is competitive. Additional sites may be initiated and 'non-productive' sites may be closed to ensure the trial timelines.

Participation in the oscillometry measurements is optional and not a prerequisite for patients to participate in the trial. The number of patients participating in the oscillometry measurements is not limited.

Every effort should be made to keep patients in the study until completion of all study procedures. Patients who discontinue after randomization may not be re-enrolled later. A record will be kept of all patients who fail to complete all study visits and their reasons for early discontinuation.

### 3.3.1 Main diagnosis for study entry

Outpatients aged 1–5 years with a history of at least one severe asthma exacerbation requiring hospitalization in the last 24 months and/or treated with 2 courses of systemic steroids before visit 1 and who are symptomatic (partly or uncontrolled) despite their current maintenance treatment with ICS are eligible for inclusion if they fulfill all the inclusion criteria (section 3.7.2) and none of the exclusion criteria (section 3.7.3).

## 3.4 Primary endpoint

**The primary efficacy endpoint** is the time to first severe exacerbations defined by hospitalization and/or at least 3 days of systemic steroids or one day of rectal prednisolone (Rectodelt®). Severe exacerbations were chosen as primary outcome because they are patient-important outcomes that have significant consequences for children, caregivers, and the health care system.

### Secondary endpoints for all patients:

- Number of severe exacerbations
- Exacerbation-free survival time defined as the time from randomization until the first severe exacerbation.
- Percentage of patients requiring systemic corticosteroid rescue for asthma during the 52-week treatment period.
- Number of hospitalizations (severe exacerbation).
- Percentage of days and episodes of  $\geq 3$  days with use of PRN salbutamol rescue medication during 52-week treatment period (non-severe exacerbation).
- Percentage of days without asthma symptoms assessed by TIPP diary App (PACD).
  - A day without asthma symptoms is defined as a day during which the patient experienced no asthma symptoms (daytime and overnight; question 1, 2, 5, 6, did not use rescue medication (salbutamol) (question 3 and 7), and had no asthma exacerbation/worsening requiring systemic corticosteroids, an unscheduled visit to a doctor's office, or hospital (question 11).
- Percentage of night-time awakenings due to asthma symptoms as assessed by the TIPP diary App.
- Health utilization defined as number of physician visits during treatment.
- Number of missed days in daycare.
- Number of asthma-related events defined by use of antibiotics.
- Evaluation of TRACK at V1, at V4 and at end of treatment.
- CGI-C at end of treatment.

### Additional secondary endpoints for children aged 4 years and older:

Only applicable for patients able to perform technically acceptable (and reproducible) pulmonary function tests.

- The forced expiratory volume in one second (FEV1) and the forced vital capacity (FVC) measured 30 minutes post IMP will be compared to pre-dosing FEV1 and FVC values at visit 2.
- Trough FEV1 and through FVC response will be determined at visit 3, visit 4, visit 5 and visit 7. Trough FEV1 is defined as the FEV1 and FVC measured approximately 24 hours after the last IMP inhalation. Response is defined as a 10% improvement in FEV1 or FVC, respectively, compared to baseline (visit 2, pre-dosing).
- Potential biomarkers for treatment response (Eosinophils, IgE, specific IgE to common allergens: birch, grass, *Dermatophagoides pteronyssinus*, *Alternaria*, *Cladosporium*, cat, dog, hen's egg, cow's milk and peanut)

**Assessment of safety:** Safety will be ensured by analysis of symptom scores and rescue medication by electronic diary, and adverse events (AEs).

### 3.5 Measures taken to minimize/avoid bias

#### 3.5.1 Randomization

A randomization list will be generated by an independent person from IZKS using a SAS® based computer program with permuted blocks without stratification factors. The randomization list assigns an identification code (medication number) to a treatment. The randomization list will be kept in safe and confidential custody at IZKS Mainz. Randomization number will be documented in the eCRF system with an identification code to a patient without knowing the treatment behind the medication number.

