#### 3.5.2 Blinding/Unblinding

In addition to the trial medication, the investigator will receive a set of sealed envelopes, comprising of one envelope for each medication number. An identical set of sealed envelopes will be held at the pharmacy of the University Medical Center Mainz. These envelopes contain information on the patients' trial medication and are to be opened only under circumstances in which it is medically imperative for diagnostic or therapeutic decisions to know which trial medication the patient is receiving. Date and reason for opening a sealed envelope must be documented by the investigator or an authorized person on the open envelope, on the eCRF, and in the medical record of the patient.

In any case, before unblinding, the investigator should consult the coordinating investigator. The randomization envelopes are not to be opened by the investigator at the end of the trial. All envelopes will be collected by the monitor of the IZKS Mainz at the end of the trial.

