### 8.1 Sample size

Sample size calculations were based on results published by Vrijlandt E et al. (33). In this study, children aged 1–5 were treated with Tiotropium 5 µg vs placebo as add-on to ICS. After 105 days, 29% of the Tiotropium 5µg group had an asthma exacerbation with pneumonia or asthma worsening, whereas 55.9% of the placebo group had an event. For the present study, it can be assumed that most patients treated with ICS + placebo will suffer from one severe exacerbation within one year, therefore a rate of 90% of placebo patients with a severe exacerbation after one year is anticipated. For the Tiotropium group, a rate of 75% is assumed. The estimation of the difference in rates between the placebo and the Tiotropium group is performed conservatively, assuming a smaller difference than observed after 105 days in the study of Vrijlandt E et al (33). The assumed dropout rate of 15% is converted into a group-loss hazard (0.16) and considered in the sample size calculation. With an event rate of 90% in the control group and 75% in the Tiotropium group and a drop-out-rate of 15%, the sample size will amount to 152 patients when applying a two-sided log-rank test with a hazard ratio of 0.60, a significance level of  $\alpha = 0.05$  and a power of 0.8. The power calculation was performed with PROC POWER in SAS® 9.4.

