### 8.3.1 Definition and analysis of primary endpoint

The primary analysis is the comparison of time to first severe exacerbation within 12 months of therapy between groups. This means especially that observations after 12 months will be censored. Dropouts because of lack of efficacy will be considered as an exacerbation. All other dropouts will be censored. The comparison will be done on a two-sided significance level of  $\alpha = 5\%$ .

The primary hypotheses are:

$$H_0: h_E/h_C = 1 \quad \text{versus} \quad H_1: h_E/h_C \neq 1$$

Where  $h_E$ ,  $h_C$  are the hazards in the experimental treatment group and the control treatment group respectively.

The time to first severe exacerbation will be analyzed by Cox regression with factor treatment group and the covariates age group and center assuming a constant hazard ratio over time. The constant hazard ratio assumption will be checked by Schoenfeld residuals. The primary analyses will be performed in the ITT population. Treatment differences will be displayed by estimates of the hazard ratios and 95% confidence intervals.

Several sensitivity analyses will be performed. The primary analysis Tiotropium + at least ICS versus placebo + ICS will be repeated additionally adjusted for LABA and LTRA use. This analysis is not primary since LABA use is not treatment independent. Additional covariates might be considered in the Cox model as well as the assessment of the per-protocol effect (both specified in the SAP). A time to recurrent event analysis is also performed. Since a substantial correlation between the events is expected a Prentice Williams and Peterson (PWP) model with the age group and center will be employed. Additionally, a Kaplan-Meier analysis including a Kaplan-Meier plot will be done.

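### The randomization list ignores center although the primary model adjusts for it; unless medication numbers already go out in whole blocks, supplying whole blocks to each site would recover most of an expected 8% loss of information at little cost

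*Protocol*

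**What the plan says.** - **Allocation.** Protocol section 3.5.1 describes one computer-generated list using "permuted blocks without stratification factors". It gives neither the block length nor a rule for dividing medication numbers among sites.
- **Analysis.** Under section 8.3.1 the primary endpoint is "analyzed by Cox regression with factor treatment group and the covariates age group and center". The recurrent-event (PWP) model in the same section also includes center.
- **Sites.** Section 3.2 says "currently 13 trial sites agreed to participate" for 152 children, an average of 152/13 = 11.7. Section 3.3 adds "Recruitment is competitive", so unequal site sizes should be expected.
- **Supply.** Section 3.5.2 says that, besides the medication, "the investigator will receive a set of sealed envelopes, comprising of one envelope for each medication number". Kits and codes are thus already held site by site.
- **Sizing.** Section 8.1 states that "the sample size will amount to 152 patients" for "a two-sided log-rank test with a hazard ratio of 0.60", two-sided 5% significance and 80% power. The calculation has no term for center.

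**The concern.** A center-adjusted comparison draws mainly on contrasts between arms inside the same center. A list that balances the arms only overall can leave individual sites lopsided. At a site with 12 children, treated as 12 independent 1:1 assignments, a split of 9:3 or worse has probability 2 × 299/4096 = 14.6%, so about 13 × 0.146 = 1.9 of 13 sites would be expected to have one. Children in a lopsided site contribute less to the adjusted estimate than they would under an even split.

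What is at stake is precision in the primary Cox model and in the recurrent-event model. Section 8.1 holds no reserve for this, and section 3.6.4 does not replace withdrawn patients.

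**Working it through.** **Inputs from the protocol.** N = 152, HR 0.60, one-year event rates of 90% and 75%, loss hazard 0.16, two-sided α = 0.05, power 0.80 (section 8.1); 13 sites (section 3.2); 12 months of follow-up (section 8.3.1).

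**Assumptions, not stated in the protocol.** 1:1 allocation; either equal sites (11–12 each) or skewed sites (29 down to 2); block lengths of 2 to 8; numbers used in list order regardless of site.

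**1. The plan's own figure.**
- Events needed (Schoenfeld): 4 × (1.960 + 0.842)² / (ln 0.60)² = 120.3, so 121.
- Control hazard: −ln(0.10) = 2.303; tiotropium hazard: 0.60 × 2.303 = 1.382.
- Event probability with loss hazard 0.16 over one year, λ/(λ+0.16) × (1 − e^−(λ+0.16)): 0.855 and 0.704, mean 0.780.
- N = 121/0.780 = 155. A Lakatos log-rank calculation gives 156.
- The stated 152 is reproduced within 3%. At N = 152 there are 118.5 expected events, and unadjusted power is 79.4%.

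**2. Information lost with the unstratified list.** With center as 12 fixed indicator terms, the expected share of treatment variance explained by center is (C − 1)/(N − 1) = 12/151 = 7.9%. Simulated site splits agree: about 92% of the information is kept for equal and skewed sites and for blocks of 2, 4, 6 and 8, with a 5–95% range of about 86–96%.

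**3. Information kept with whole blocks per site.**

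| Block length | Equal sites | Skewed sites |
|---|---|---|
| 2 | 99.8% | 99.4% |
| 4 | 99.8% | 98.7% |
| 6 | 99.8% | 98.3% |
| 8 | 98.4% | 97.8% |

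**4. Power by formula at N = 152.** Power = Φ(|ln HR| × √(D × k)/2 − 1.96), where D = 118.5 and k is the share of information kept.
- k = 1: Φ(0.820) = 79.4%.
- k = 0.921 (unstratified list): Φ(0.708) = 76.0%.
- k = 0.987 (site blocks of 4, skewed sites): Φ(0.802) = 78.9%.

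The gap is about 3 points.

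**5. Simulated center-adjusted Cox fits** (4,000 trials per scenario, center as indicators, age group left out):

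| Scenario | Unstratified list | Site blocks |
|---|---|---|
| Equal sites, blocks of 4 | 78.1% | 81.7% |
| Skewed sites, blocks of 4 | 77.2% | 81.0% |
| Skewed sites, blocks of 6 | 78.1% | 81.0% |
| Equal sites, blocks of 4, assumed center SD 0.3 on the log hazard | 77.1% | 80.3% |
| Skewed sites, blocks of 4, assumed center SD 0.3 | 77.1% | 79.8% |

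The gap runs from 2.7 to 3.8 points. These rates come from a slightly anticonservative test: with no treatment effect, the indicator model rejected in about 6% of trials under either scheme. The difference between columns is therefore more reliable than the levels.

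**6. Other ways of entering center.**
- Five pooled center groups: 4/151 = 2.6% lost, about 1 point of power.
- Random center effect with the same assumed SD of 0.3: a generalized least squares approximation keeps 96.4% (equal sites) to 96.9% (skewed sites). Power falls from 80.0% to about 78.5–78.7%, a loss of about 1.5 points or less.

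**The case against.** The strongest reply is that the protocol does not show that the loss occurs. Section 3.5.1 says how the list is generated, not how it is distributed. An unstratified list shipped in whole blocks fits both 3.5.1 and 3.5.2 and would already be the remedy. Likewise, 8.3.1 names center as a covariate without saying how it is coded, and coding or pooling of small sites is commonly settled in the SAP. Both points stand, and they make the 8% conditional. They do not remove the case for a change: if blocks are already kept together by site, 3.5.1 should say so, and if they are not, the gain is available cheaply.

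Three stronger readings are tempting but unsupported.
- *That the trial falls 3 points short of its stated 80%.* The 3 points are a gap to a site-blocked list. Against the unadjusted 79.4% at N = 152, simulated power under the present plan is only 1–2 points lower when centers do not differ, partly because the indicator model overstates the effect slightly (mean HR about 0.575 for a true 0.60) and rejects a little too often.
- *That the two sections contradict each other or that the analysis is invalid.* Unstratified blocks with covariate adjustment are a valid combination. Section 3.5.1 claims no center balance, and 8.3.1 does not claim to mirror the randomization.
- *That the change is free.* Small sites end on incomplete blocks. Emergency envelopes sit at every site, so one code break says more about neighbouring allocations when blocks are site-specific. Double-blinding and undisclosed block lengths keep this risk small.

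**Conclusion.** The point holds as a cheap gain in efficiency. If medication numbers are not already sent out in whole blocks and center enters as separate fixed terms, the expected cost is about 8% of the information on the treatment effect. That figure is an average over possible allocations, with a 5–95% range of about 4–14%. It corresponds to power of about 76% rather than 79% by formula at N = 152. The loss shrinks to about 1 to 1.5 points if small sites are pooled or center is a random effect, and it largely disappears if whole blocks already go to sites. Nothing here indicates bias.

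The finding is no reason to drop center from the model. With an assumed center SD of 0.3, the unadjusted analysis on the unstratified list had simulated power of only 74.4–75.0%, against 77.1% adjusted. The mismatch is better resolved on the allocation side. The change is worth making but is not essential to the validity of the trial.

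**What to change.** - **Section 3.5.1.** State: *Randomization is stratified by center. Each site is supplied with whole permuted blocks of medication numbers, used in sequence; block lengths are not disclosed to the sites.* Keep the blocks short, because long blocks at small sites give back part of the gain.
- **Section 8.3.1.** State that the adjustment for center reflects the randomization.
- **If numbers have already been shipped.** Apply the rule to every new shipment and every newly opened site. If whole blocks were already being sent, correct the description in 3.5.1 to say so.

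**Cost.** One protocol sentence in each section and a shipping rule, with no additional children, visits or procedures. Kits become tied to sites, which reduces flexibility under competitive recruitment. Incomplete last blocks leave about 0.2–2% of the information unrecovered and may leave an overall imbalance of a few children. Guessing neighbouring allocations after a code break becomes slightly easier.
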